Sites with simple randomised sampling employ a random-walk sampling method.^41^ With the simple randomised sampling strategy, a random number generator (eg, dice or random number generating application) with set parameters (ie, less than 20, less than 30 and so on) determines which households to survey (and, if needed, the direction of the random walk). Surveys are administered to each household corresponding to the random number, such that a random draw of the number 3 indicates that every third household should be sampled. For sites using a cluster-randomised sampling strategy, the region is first mapped using a grid or satellite imagery (eg, Google Maps) to identify population density based on the number of habitable structures. Clusters are selected from this grid, and households within clusters are randomly sampled in proportion to structure or population density using a random number generator, similar to the simple randomised sampling strategy. Cluster randomisation is preferred, but simple random sampling is used when cluster data are not available, typically in sparsely populated settings.

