### Reliability

To test for the reliability (internal consistency) of the items, we will estimate Cronbach’s alpha for both site-specific and aggregate-level data.^59^ The Rasch reliability statistic is analogous to Cronbach’s alpha. In our analyses, we will consider reliability to be ideal if it is greater than 0.80.^59^

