### Validity

We will examine three types of validity: predictive, convergent and discriminant validity. Predictive validity is ‘the extent to which a measure predicts the answers to some other question or a result which it ought to be related with’.^60^ Using both linear regression and structural equation models, we will test for predictive validity by regressing HWISE Scale scores on eg, food insecurity, perceived stress and income.

Convergent validity is the ‘degree to which scores on a studied instrument are related to measures of other constructs that can be expected on theoretical grounds and accumulated knowledge to be close to the one tapped into by this instrument’.^48^ To test for convergent validity, we will assess the relationships between HWISE Scale scores and individual items that have shown to be closely related to the concept of water insecurity. Specifically, we will use linear regression to examine the strength of the relationships between HWISE Scale scores and eg, time to water source, number of trips to water source and amount of money spent purchasing water. Larger correlation and regression coefficients and smaller SD of residuals will be indicative of support for convergent validity.

Discriminant validity is the ‘degree to which scores on a studied instrument are differentiated from behavioral manifestations of other constructs’.^48^ A test of differentiation between ‘known groups’ will be conducted using the Student’s *t*-test^34 48^; these groups will be based on accumulated knowledge. We will determine the distribution of household water insecurity scores across known groups, eg primary source of drinking water (improved vs unimproved sources), water treatment (treated vs untreated), gender of household head (male vs female) and injuries associated with water acquisition (yes vs no).^4 5 10 24 61^ Under the Rasch measurement model, differentiating between known groups will also be conducted using differential item functioning. We will determine whether each scale item performs differently in each of the subgroups. Differential item functioning is attained when the probabilities of an item being endorsed is unequal for the two subgroups.^10 62^

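### Student's t-test and plain linear regression assume independent respondents, but cluster sampling is the preferred design and is used at 12 to 14 of the 28 sites

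*Protocol article*

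**What the plan says.** **Tests.** The Validity section (Phase 3) fixes the known-groups method: "A test of differentiation between ‘known groups’ will be conducted using the Student’s" t-test. Its example groupings are improved against unimproved drinking-water source, water treatment, gender of household head, and injury during water acquisition. For convergent validity, "we will use linear regression to examine the strength of the relationships between HWISE Scale scores and eg, time to water source" and similar measures. For predictive validity, "Using both linear regression and structural equation models, we will test for predictive validity by regressing HWISE Scale scores on" food insecurity, perceived stress and income. None of these sentences mentions a cluster term, a site term, survey weighting or a robust variance.

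**Design.** Participant selection describes the clustered sites thus: "Clusters are selected from this grid, and households within clusters are randomly sampled in proportion to structure or population density". It says that cluster selection is preferred, with simple random sampling used where cluster data are lacking.

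**Reliability.** "we will estimate Cronbach’s alpha for both site-specific and aggregate-level data", and "we will consider reliability to be ideal if it is greater than 0.80". The benchmark is not tied to either level.

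**Level of judgement.** The closing paragraph of the Validity section asks that each item be reliable, and contribute to all three kinds of validity, in each site.

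**The concern.** Households in one cluster tend to share wells, standpipes, vendors and supply interruptions. Their water insecurity scores are therefore likely to be correlated, and so are some of the labels against which the score is tested. A Student's t-test has no place for a cluster-robust variance or a site term, so naming it is a choice and not merely silence. When score and label both cluster, the test treats repeated local information as independent evidence. Known-groups differences and regression coefficients would then be reported with intervals that are too narrow.

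Two related matters follow. If respondents from different sites are combined in one test without a site term, a group difference can arise from differences between sites. And an alpha computed on combined data includes between-site differences in item means, so it can look better than reliability within any site.

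**Working it through.** **1. Is there a figure of the plan to reproduce?** The target of 250 per site is justified by stability of the factor pattern. It comes with no error rate, effect size or design effect, so it cannot be recomputed. As a check that Table 3 was read correctly, its site sizes sum to 4815 for Module Version 1 (stated: 4817) and 3309 for Version 2 (stated: 3310).

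**2. How much of the sample is clustered?** From Table 3:
- Labelled cluster random: Lilongwe 302, Arua 250, Morogoro 300, Labuan Bajo 279, Dushanbe 225, Ceará 254, Mérida 250, Honda 196, Acatenango 101, Beirut 573, Kathmandu 263, Punjab 235. That is 12 of 28 sites and 3228 people.
- Adding Kahemba (cluster trial, 392) and Lagos (multistage, 239): 14 sites and 3859 people.
- Denominator: 4815 + 3309 = 8124. Singida counts as 564 instead of 1006 (Table 3 footnote), giving 8124 − 1006 + 564 = 7682.
- Shares: 3228/7682 = 42%; 3859/7682 = 50%.

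**3. Effect within a clustered site.** The article gives neither cluster size (m) nor ICC, so both are assumed.

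Label constant within clusters: DEFF = 1 + (m − 1) × ICC. Actual type I error = 2 × [1 − Φ(1.96/√DEFF)].

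| m | ICC | DEFF | Type I error | Effective n of 250 |
|---|---|---|---|---|
| 10 | 0.01 | 1.09 | 6.0% | 229 |
| 10 | 0.05 | 1.45 | 10.4% | 172 |
| 10 | 0.10 | 1.90 | 15.5% | 132 |
| 10 | 0.20 | 2.80 | 24.1% | 89 |
| 25 | 0.05 | 2.20 | 18.6% | 114 |
| 25 | 0.10 | 3.40 | 28.8% | 74 |

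Label varying within clusters: DEFF = 1 + (m − 1) × ICC of score × ICC of label. With m = 10 and score ICC 0.10:
- label ICC 0: DEFF 1.00, type I error 5.0%
- label ICC 0.1: DEFF 1.09, type I error 6.0%
- label ICC 0.3: DEFF 1.27, type I error 8.2%

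At score ICC 0.20 and label ICC 0.3, DEFF is 1.54 and the error 11.4%.

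**4. If a test were pooled without a site term.** This was simulated with the 28 Table 3 site sizes (Singida 564), no effect within any site, and 1000 runs per setting. With an assumed score-level site ICC of 0.05 to 0.30 and a label site ICC of 0.1 to 0.3, the pooled t-test rejected in 21% to 69% of runs. With a label site ICC of 0 it rejected in about 5%. The site-adjusted estimate rejected in 3% to 6% throughout.

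**5. Can the contrast be run in every site?** Table 2 gives Kahemba 99.7% surface water: 0.997 × 392 ≈ 391, leaving about one respondent. However improved and unimproved are defined, there is essentially no second group there.

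**6. Aggregate alpha.** Aggregate alpha = (within-site alpha + b)/(1 + b), with b = ICC/(1 − ICC) and ICC the assumed share of score variance lying between sites. From 0.70 within site:
- ICC 0.1: (0.70 + 0.111)/1.111 = 0.73
- ICC 0.2: (0.70 + 0.25)/1.25 = 0.76
- ICC 0.3: (0.70 + 0.429)/1.429 = 0.79

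**The case against.** The case against is substantial, and much of it stands.

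- **Pooling.** A reader might infer that the validity results will mostly reflect differences between sites. The article does not support that. It never says that the tests are pooled, it judges validity and reliability in each site, and it gives no between-site variance. It also handles site structure in the measurement model through multigroup confirmatory factor analysis and alignment. Step 4 applies only if a pooled test is run without a site term.
- **Condensed article.** Variance estimation is often left to a fuller plan, so to say that clustering is ignored would be too strong. This answers the silence about standard errors, but not the naming of a test that cannot accommodate clusters.
- **Size.** The larger error rates need a label that is constant within clusters. Treatment, gender of household head and injury can differ between neighbours, and the inflation is then small.
- **Consequence.** Convergent validity is judged on the size of coefficients and the residual SD, where standard errors matter less. No stated decision turns on a known-groups p-value.
- **Alpha.** A reader might infer that pooling alone can carry the scale past 0.80. Site-specific alpha is reported alongside, 0.80 is called ideal and not a pass mark, and step 6 stays below 0.80 from a within-site 0.70. Nor is this a standard-error problem, since alpha is a coefficient.
- **Concentration of unimproved sources.** A reader might tally Table 2 and conclude that unimproved sources sit almost wholly in a few African sites. The article does not define the classification: tanker and vendor water (Rajasthan 55.2% tanker, Beirut 54.5% vendor) could fall either way, and the Other category reaches 33.6% in Mérida. That tally is not relied on here.

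**Conclusion.** The point holds in a limited form. The named t-test and linear regression do not match the preferred sampling design, which covers 12 of 28 sites by label, or 14 if the cluster trial and the multistage sample are counted; half the sites is true only on the wider count. Running the tests site by site does not remove the problem, because the clusters lie within sites.

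Standard errors will be too small where score and label both cluster. With 10 households per cluster, the nominal 5% becomes about 10% to 24% for a cluster-constant label (ICC 0.05 to 0.20) and about 5% to 8% for one that varies within clusters (score ICC 0.10, label ICC 0 to 0.3). These sizes rest on assumed cluster sizes and ICCs; the direction needs only positive clustering of both. That drinking-water source clusters by area is plausible but not documented.

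Site confounding is conditional on a pooled test without a site term. Inflation of aggregate alpha is secondary.

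**What to change.** 1. State for each validity test whether it is run within site, pooled, or both.
2. Replace the t-test with the equivalent regression of HWISE score on the group indicator. At sites with clustered sampling, use cluster-robust or survey standard errors (Stata svy, Mplus TYPE=COMPLEX) for this and for the convergent and predictive regressions.
3. In any pooled analysis, include site fixed effects, or random site intercepts and slopes.
4. Set a minimum size for the smaller group and report site-specific contrasts only where both groups reach it; Kahemba's drinking-water contrast would not.
5. Apply the 0.80 benchmark to site-specific alpha or to a pooled within-site alpha (items centred at site means), and keep aggregate alpha as description.

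The cost is a few sentences and a few lines of code in Stata and Mplus, which the article already names. Cluster identifiers must have been retained, which should be confirmed for each clustered site. The price in results is wider intervals and a slightly less favourable alpha.

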### Assess measurement equivalence

Measurement equivalence concerns the extent to which the psychometric properties of the observed indicators are generalisable across groups or over time.^52–55^ It holds ‘when a test measures a construct in the same way regardless of group membership and is violated when individuals from different groups respond to the test in a dissimilar manner’.^39^ A violation of equivalence implies our inability to make comparisons about the measurement and meaning of scale values across groups (eg, sites, cultures and languages).^39^ To determine measurement equivalence across sites using Module Versions 1 and 2, we will use multigroup confirmatory factor analysis and alignment optimisation.^56–58^

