In sum, selection of the set of items to be included in the final scale will be based on several criteria. The criteria for inclusion of an item are: reliable in each site, fits theoretically and empirically with concepts related to water insecurity, has face and content validity in each site, shows equivalent measurement and meaning across sites and contributes to predictive, convergent and discriminant validity in each site.^63^ We anticipate that not every item will meet each criterion perfectly, and judgement about tradeoffs of which items to include will be required. These judgements will be made considering the additional criteria of having a diversity of items in the final scale that cover as many facets of water insecurity as reasonably possible. We anticipate that the final scale will have fewer than 20 items, which will reduce the likelihood of participant fatigue and make its widespread application more feasible.

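### Differential item functioning is listed as known-groups evidence and defined without conditioning on water insecurity; it should be a check for item bias at equal person measure

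*Protocol article*

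**What the plan says.** The Validity section (Phase 3) treats known groups in its paragraph on discriminant validity. The score-level test comes first: "A test of differentiation between ‘known groups’ will be conducted using the Student’s" t-test. On the choice of groups it says that "these groups will be based on accumulated knowledge". The examples are improved versus unimproved drinking-water source, treated versus untreated water, gender of household head, and injury linked to fetching water.

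DIF follows as a second method: "Under the Rasch measurement model, differentiating between known groups will also be conducted using differential item functioning". The item-level question is put neutrally: "We will determine whether each scale item performs differently in each of the subgroups". The definition is: "Differential item functioning is attained when the probabilities of an item being endorsed is unequal for the two subgroups".

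Two other places bear on this. The section on measurement equivalence says that equivalence "is violated when individuals from different groups respond to the test in a dissimilar manner". The summary of inclusion criteria that closes the Validity section asks that an item "shows equivalent measurement and meaning across sites and contributes to predictive, convergent and discriminant validity in each site".

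**The concern.** DIF means that respondents at the same level of the latent trait, but in different groups, have different probabilities of endorsing an item. It describes an item that does not measure both groups alike. The article departs from this in two ways.

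- **Definition.** Without the condition of equal trait level, the sentence describes an ordinary group difference in endorsement. Known groups are chosen because they are expected to differ in water insecurity. If they do, a sound item should be endorsed at different rates, so the stated definition cannot tell a working item from a biased one.
- **Role.** DIF is presented as a further way to differentiate known groups. Even when correctly conditioned, it says nothing about whether scale scores separate the groups.

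What is at stake is the choice of items. Contribution to discriminant validity is an inclusion criterion, and DIF is filed under discriminant validity. A reader following the text could fault a fair item because its endorsement differs between groups, or credit a biased item because it does. These are alternative misreadings of one result, and would not both befall the same item.

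**Working it through.** The article gives no significance level, effect size or DIF threshold, so there is no planned figure to reproduce. The calculations below only show how the literal definition behaves.

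**Inputs**
- From the article: a target of 250 per site (Participant selection) and a final scale expected to have fewer than 20 items (Validity).
- Assumed: dichotomous Rasch items with no DIF, latent SD of 1 within each group, two-sided 5% level, group differences δ of 0.3, 0.5 and 1 logit, equal groups of 125 (half of 250). The real items have five frequency categories.

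**1. The literal definition applied to fair items**

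Endorsement probability in a group with mean μ for an item of severity b is p(μ, b) = ∫ φ(θ − μ) / (1 + exp(−(θ − b))) dθ, with μ = ±δ/2.

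The chance that a two-proportion test flags the item is approximately Φ[(|p1 − p2| − 1.96·s0) / s1], plus a negligible opposite tail. Here s0 is the pooled standard error and s1 the unpooled one.

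Worked case, δ = 1 and b = 0: p1 = 0.602 and p2 = 0.398, a difference of 0.204. s0 = √(0.5 × 0.5 × 2/125) = 0.0632 and s1 = √(2 × 0.602 × 0.398/125) = 0.0619. So (0.204 − 1.96 × 0.0632)/0.0619 = 1.29, and Φ(1.29) = 0.90.

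| δ (logits) | p1 / p2 at b = 0 | p1 / p2 at b = −1 | Fair items flagged, 125/125 | Fair items flagged, 225/25 |
|---|---|---|---|---|
| 0.3 | 0.531 / 0.469 | 0.723 / 0.669 | 15-16% | 7-10% |
| 0.5 | 0.551 / 0.449 | 0.739 / 0.651 | 33-37% | 13-18% |
| 1.0 | 0.602 / 0.398 | 0.779 / 0.602 | 86-90% | 39-50% |

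Ranges cover b = −1, 0 and 1. The 225/25 split is included because Table 2 shows very uneven water sources at some sites, for example 89.4% piped water in Pune.

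**2. The literal definition against a conditional test**

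A simulation used 15 DIF-free items with severities from −2 to +2 and two equal groups. It compared the unconditional test with a Mantel-Haenszel test stratified on total score.

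| δ (logits) | Unconditional, n = 250 | Unconditional, n = 1000 | Conditional, either n |
|---|---|---|---|
| 0.3 | 15% | 39% | about 5% |
| 0.5 | 31% | 83% | about 5% |
| 0.8 | 63% | 99% | about 5% |

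The conditional test keeps its nominal rate. The unconditional one increasingly flags fair items as the true group difference or the sample grows.

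**3. The reverse error**

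In the same setting one item was given a bias of 0.5 logits, opposite in direction to a true group difference of 0.5 logits. The unconditional rule flagged it 5% of the time, and the conditional test 36% (n = 250) or 90% (n = 1000).

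**4. Is DIF evidence that scores separate groups?**

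With no true group difference and one item biased by 0.8 logits (n = 250), that item was flagged 72% of the time unconditionally and 74% conditionally. The comparison of total scores rejected only about 6% of the time. Clear DIF can therefore go with no separation of the groups by the scale, even when the DIF test is done properly.

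**The case against.** The strongest reply is that nobody plans an unconditional two-proportion test. The article places the analysis under the Rasch model, and the Analytic strategy section assigns Rasch work to WINSTEPS. A Rasch DIF analysis compares item difficulty given the person measures, so the conditioning may be built in and one sentence merely loosely worded. This stands as far as it goes: if the routine conditions, the false flags in steps 1 and 2 do not arise. It does not cure the definition as printed, and it does not turn DIF into known-groups evidence, as step 4 shows.

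A reader might infer that the plan counts item bias as validity. The article does not say so. No rule says that DIF supports an item or removes one, and the item-level question is neutral. The rules under Item reduction rest on missingness, correlations, Rasch fit and residual correlation. The inference comes only from the placement of DIF and the words used for it.

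A reader might also infer that the known-groups conclusion is wrong in any event. That is not supported either, because the t-test on scores stands on its own and DIF does not alter it.

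Finally, the measurement-equivalence section might be read as a direct contradiction. It concerns mainly sites, cultures and languages, tested by multigroup factor analysis and alignment, whereas the DIF sentences concern household subgroups. The tension is one of principle: dissimilar responding counts against a scale in one section and appears as a means of differentiation in the other.

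**Conclusion.** The point holds as an error in a stated definition and a stated purpose, so it is not detail left to a fuller document. DIF is defined without conditioning on water insecurity and is assigned to known-groups differentiation; both statements need correcting.

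The practical consequence depends on the routine that is run. With the literal definition, roughly 15%, 35% and 86-90% of fair items would be flagged at 0.3, 0.5 and 1 logit with 125 per group, and about half those rates with a 225/25 split. These figures rest on dichotomous items, assumed severities and assumed group differences, and on a test that the article does not explicitly schedule, so they are illustrative only. With a conditional routine the flags are about 5%, and what remains is the misplaced role. Because no decision rule is given and the final choice of items is left to judgement, the residual risk is a DIF result read in the wrong direction.

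**What to change.** 1. Define DIF as unequal probability of endorsement (or of a response category, since the items have five) for respondents with the same Rasch measure of water insecurity.
2. Move it from known-groups validity to item reduction or measurement equivalence, and state that DIF counts as evidence against an item. The subgroups already named in the Validity section can be kept.
3. For known groups under the Rasch model, compare mean person measures between the groups, alongside the planned t-test on scale scores.

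Adding DIF by site and module version is optional, since the measurement-equivalence section already tests equivalence across sites using both versions.

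The cost is rewording a few sentences. The software is already in the plan and no new data are needed.

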### Midstudy evaluations

In August 2017, 5 months after data collection began in 8 of 16 Module Version 1 sites, HWISE RCN members met at Northwestern University to review and discuss data received to date and thematically sort HWISE items. This led to the reduction and refinement of HWISE for the second wave of survey implementation (Module Version 2), which is being administered across 12 sites (table 2 and 3). In February 2018, HWISE RCN members involved in scale validation met at McGill University to review Module Version 2 responses to date and further refine the survey. Members of the analytic team also hold regular conference calls to review subsequent results and complete the scale validation process.

